### Participant drop-outs

The participant can decide to discontinue treatment at any time for any reason.The patient is non-compliant.The patients experiences a serious AE.

Drop-outs and withdrawals from the trial will be recorded throughout the intervention and follow-up periods. Their data will be collected in the case report form but will not be used for the final statistical analysis.

### Sample size

The ratio of cases between the JTW group and the placebo group is set to 1:1; this study is designed to achieve a statistical power of 80% (two-sided type-1 error of *α* = 5%, *β* = 20%). Based on previous clinical practice [33, 34], we assume a treatment success rate of 40% in the placebo group and 70% in the JTW group over 7 days. The sample size is calculated using the following formula:
$$ N={\left[{\Phi}^{-1}\left(\alpha \right)+{\Phi}^{-1}\left(\beta /2\right)\right]}^2\times \left({\pi}_e+{\pi}_0\right)\left(100-\left({\pi}_e+{\pi}_0\right)/2\right)/{\left({\pi}_e-{\pi}_0\right)}^2 $$where Φ is the cumulative distribution function of the standard normal distribution, and *π*_*e*_ and *π*_0_ are the success rate in the experimental and control groups, respectively. Considering a 20% drop-out rate, a sample size of *N* = 49/(1–0.2) = 62 is needed for each group.

Thus, under the assumptions of a success rate of 70% for treatment and 40% for placebo, and a non-compliance rate of 20%, the sample size required to have at least 80% power of detecting a difference between the two groups at a two-sided alpha level of 5% is 124 participants.

### Data management and monitoring

The experimental data will be carefully saved in Microsoft Access, a database management system (DBMS) from Microsoft. To guarantee the data quality, data will be input and checked twice by two researchers. During the study, the First Affiliated Hospital of Wenzhou Medical University is responsible for making regular visits (once a month) to review trial conduct; the Ethics Committee will monitor for protocol violations monthly. There was no conflict of interest with the sponsors or researchers.

In addition, confidentiality of participants’ data is ensured by using participants’ IDs rather than identifiable information in the dataset (i.e. coding) and by storing the document linking the IDs to the identifiable information separately and securely. Only researchers directly involved in the analysis of the randomized controlled trial (RCT) will have access to the final trial dataset, which will only contain coded data. After data collection and before data storage, all outcomes are manually double-checked by the research staff. The safety, progress, study integrity, and design aspects will be monitored at various meetings by the research team involved in this study.

### Statistical analysis

We will use two-sided *p* values for the primary outcome and for all secondary outcomes and safety variables. For the primary outcome, we will use Fisher’s exact test to test the hypothesis at null: the treatment has the same efficacy as the placebo. For each secondary outcome, defined as the value difference between baseline and end-of-intervention, we will use the following tests: (1) t-test for the continuous PSG variables; Chi-square test for the categorical PSG variables; (2) t-test for the blood-level adenosine and melatonin; (3) t-test for the GABA/Cr ratio; and (4) Wilcoxon rank sum test for the Disharmony Score of Heart and Kidney. For safety evaluation of JTW, a two-sided t-test will be applied to each safety measurement after data normalization.

We define the analysis population as the enrolled participants who have successfully completed the trial. We will characterize the types of individuals who have missing data to better understand the nature the missing mechanisms. We will use statistical models to impute missing values if the assumption of missing at random is met. This can preserve and utilize the information of the non-missing values.

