#### Secondary outcomes

##### Polysomnography

Polysomnography (PSG) will be taken twice, at both the baseline and the end of the drug intervention. On the first night, participants will adapt themselves to the laboratory environment. On the second night, participants will be placed on PSG monitoring to record the multiple physiological sleep parameters. The parameters [20, 21] will include total sleep time, sleep efficiency, sleep latency, rapid eye movement (REM) stage latency, wake after sleep onset, and the time duration of the particular sleep stages (such as N1, N2, N3). The mean changes of all the parameters from the baseline to the end of the drug intervention will be used to measure the changes in sleep quality.

PSG is considered the gold standard for scoring sleep disorders. The scoring of sleep and arousals relies on visual inspection of continuous surface electroencephalography (EEG), electromyography (EMG), and electrooculography (EOG) during PSG and then divides human sleep into five stages: wakefulness (W); REM; non-rapid eye movement (NREM); and N1, N2, and N3 [22]. The American Academy of Sleep Medicine (AASM) defined the quantitative reference standard in PSG for adult insomnia as follows [23]: sleep latency ≥ 30 min; total sleep time < 390 min; number of wake after sleep onset (WASO) ≥ 2 or time of WASO ≥ 40 min; time in N1/total sleep time > 60%; time in N2 / total sleep time > 60% or time in N3/total sleep time < 10%, or time in REM / total sleep time < 20%. A higher or lower score corresponds to more severe symptoms.

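### Continuous secondary outcomes and the Disharmony score are tested on raw baseline-to-end differences; adjusting for the baselines already collected would be more precise at no data cost

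*Protocol article*

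**What the plan says.** The Statistical analysis section of the protocol article assigns a test to each outcome. For the secondary outcomes it states: "For each secondary outcome, defined as the value difference between baseline and end-of-intervention, we will use the following tests". The list includes a t-test for the continuous PSG variables, a Wilcoxon rank sum test for the Disharmony score, and, for the laboratory and spectroscopy outcomes, "2) t-test for the blood-level adenosine and melatonin; (3) t-test for the GABA/Cr ratio". The Polysomnography section takes the same line: "The mean changes of all the parameters from the baseline to the end of the drug intervention will be used".

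For the responder endpoint the section says: "For the primary outcome, we will use Fisher’s exact test".

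No covariate or regression model is named for any treatment comparison. Statistical models are mentioned only for imputing missing values. The Design paragraph of the abstract and the outcome sections show that baseline values are collected for all these outcomes.

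**The concern.** A two-sample t-test on end minus baseline treats the slope of the end value on the baseline value as exactly 1. Repeated biological measurements usually have a smaller slope. The change score then carries baseline noise that a fitted slope would remove, and intervals are wider than the data require.

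The change score also does not remove a chance baseline difference between arms. If the slope is β and the arms differ by D at baseline, the change-score contrast moves by (β − 1)D in that realised sample. ANCOVA removes this term.

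The Sample size section covers only the responder rate. The PSG, GABA/Cr, adenosine and melatonin comparisons have whatever power about 49 completers per arm happen to give, so precision matters most there. PSG and spectroscopy are also burdensome to obtain, and their baseline measurements will already be in hand.

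**Working it through.** **Inputs from the article (Sample size section).** "we assume a treatment success rate of 40% in the placebo group and 70% in the JTW group over 7 days"; "The ratio of cases between the JTW group and the placebo group is set to 1:1"; two-sided α of 5% and 80% power; 20% drop-out. **Assumed:** ρ, the within-arm correlation between baseline and end value, which the article does not give; values from 0.3 to 0.8 are shown.

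**1. The plan's own figure.** The uncorrected two-proportion size is [1.96·√(2·0.55·0.45) + 0.8416·√(0.7·0.3 + 0.4·0.6)]² / 0.30² = 41.97 per arm. The continuity correction gives (41.97/4)·[1 + √(1 + 4/(41.97·0.30))]² = 48.4, so 49. Then 49/0.8 = 61.25, so 62 per arm and 124 in total. This matches the stated numbers.

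**2. Precision of the continuous secondary outcomes.** Write end = β·baseline + residual within arm.
- Variance of the change score: residual variance + (1 − β)²·Var(baseline).
- Variance after ANCOVA (large sample): residual variance alone.
- The ratio is therefore never above 1, and equals 1 only when β = 1.
- With equal variances σ² at both times, β = ρ. The change-score variance is 2σ²(1 − ρ), the ANCOVA variance is σ²(1 − ρ²), and the ratio is (1 + ρ)/2.

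For a comparison with 80% power by change-score t-test, power under ANCOVA is Φ(2.8016/√ratio − 1.96). The number per arm that matches the precision of 49 by change score is 49 × ratio, rounded up.

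| Assumed ρ | Variance ratio | Power if t-test has 80% | Per arm to match 49 |
|---|---|---|---|
| 0.3 | 0.65 | Φ(1.515) = 93.5% | 32 |
| 0.5 | 0.75 | Φ(1.275) = 89.9% | 37 |
| 0.7 | 0.85 | Φ(1.079) = 86.0% | 42 |
| 0.8 | 0.90 | Φ(0.993) = 84.0% | 45 |

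Estimating the slope costs one degree of freedom (95 instead of 96 with 98 completers), which is negligible. The formula does not apply directly to the Wilcoxon test on the Disharmony score, so no figure is given for that outcome.

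**3. The primary test, for comparison.** Exact enumeration at 49 per arm and 70% against 40% gives Fisher's test 81.5% power. Its true size is 3.0% to 3.3% for common success rates of 40% to 70%. Boschloo's test has maximum size 4.9% and power 85.6%. The uncorrected chi-square test has power 86.6%, but its size is about 5.3% at a common rate of 55%.

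**4. Baseline PSQI in the primary analysis.** A simulation with 49 per arm and 2,000 runs gives a baseline-adjusted logistic likelihood-ratio test about 86% power if baseline is not prognostic. Power is about 87%, 90% and 93% for assumed log odds ratios of 0.5, 0.8 and 1.2 per SD.

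**The case against.** The strongest reply is that nothing here is wrong. Change-score tests are valid under randomization, the outcomes are secondary in a trial that calls itself a pilot, none of them is powered, and the gain depends on a correlation the article does not give. At ρ = 0.8 it is only 4 points. Adjusted analyses might also sit in an analysis plan that is not shown. The first part stands and sets the size of the point. The last part has less force, because the article does not leave the test open: it names one for each outcome. The direction of the gain does not depend on ρ.

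A reader might infer three stronger claims that the article does not support.

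- **That Fisher's test is an error, or shows what unused baselines cost.** The Sample size section claims "at least 80% power of detecting a difference between the two groups at a two-sided alpha level of 5% is 124 participants". The 49 completers per arm behind that total match the continuity-corrected formula, which allows for Fisher's conservatism, and the test delivers 81.5%. The contrast of 81.5% with 86.6% for chi-square compares two unadjusted tests and says nothing about baseline values. Any gain from adjusting for baseline PSQI depends on how strongly it predicts response, which is not stated.
- **That entry thresholds on PSQI and the Disharmony score make matters worse.** Truncation on baseline leaves a linear slope unchanged and shrinks the baseline variance, so the penalty (1 − β)²·Var(baseline) falls. Take β = 0.5, unit variances before selection and a cut at the mean. The baseline variance becomes 0.363 and the ratio 0.75/(0.75 + 0.25 × 0.363) = 0.89 instead of 0.75. PSG, adenosine, melatonin and GABA/Cr are not entry criteria in any case.
- **That the planned estimates are biased.** Over repeated randomizations the change-score contrast is unbiased, and its standard error already reflects chance imbalance. The issue is conditional on the imbalance that happens to occur.

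The categorical PSG variables, planned for chi-square tests, are outside this point.

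**Conclusion.** The point holds as one of efficiency, limited to the continuous secondary outcomes and the Disharmony score. For the continuous outcomes, the planned t-test gives up 10% to 35% of the variance over assumed correlations of 0.8 down to 0.3. That is about 4 to 14 percentage points of power for a comparison that would otherwise have 80%. These sizes rest on the assumed ρ, equal baseline and end variances, and a linear relation between baseline and end value. For the Disharmony score the same reasoning applies, but the gain is not quantified. There is no inflation of type 1 error, no unconditional bias and no shortfall in the primary outcome's planned power. The change is worth making because it costs almost nothing.

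**What to change.** In the Statistical analysis section, before the blinding codes are revealed:

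- For each continuous secondary outcome (PSG parameters, adenosine, melatonin, GABA/Cr), replace the t-test on the difference with ANCOVA of the end value on arm and that outcome's own baseline. Use a log scale where the distribution is skewed. Report the adjusted difference (a ratio if logged) with its 95% CI.
- For the Disharmony score, replace the Wilcoxon test on the difference with a baseline-adjusted rank analysis or a proportional-odds model with baseline as covariate.
- Align the sentence on mean changes in the Polysomnography section. Mean changes can stay as descriptive summaries.

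Optional: replace Fisher's test with Boschloo's, which keeps size within 5% (maximum 4.9%) and raises power from 81.5% to 85.6% at 49 per arm. A logistic model with baseline PSQI could be a supporting analysis.

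The cost is revised wording and a few lines of programming, with no new data, visits or participants.

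### The efficacy analysis is limited to completers and bars the collected data of participants who withdraw, are non-compliant or have a serious adverse event, so the comparison is no longer protected by randomisation

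*Protocol article*

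**What the plan says.** Under Statistical analysis, the protocol article names one analysis population: "We define the analysis population as the enrolled participants who have successfully completed the trial". No all-randomised set is named.

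Under Participant drop-outs, three reasons are listed: the participant's own decision, a serious adverse event, and "The patient is non-compliant". Of these participants the section says: "Their data will be collected in the case report form but will not be used for the final statistical analysis".

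Statistical analysis also promises to describe who has missing data, and adds: "We will use statistical models to impute missing values if the assumption of missing at random is met".

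Under Sample size, "we assume a treatment success rate of 40% in the placebo group and 70% in the JTW group over 7 days". The 49 per group needed for analysis is raised to 62 for a 20% loss, which that section calls drop-out in one place and non-compliance in another. Study design describes a parallel-group randomised superiority trial. The primary outcome is the proportion of participants with a PSQI reduction rate of at least 25%, compared by Fisher's exact test.

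**The concern.** All three drop-out reasons arise after randomisation, and each may be influenced by treatment: tolerability, perceived lack of benefit, adverse events. Selecting on them means that the groups compared are no longer those that randomisation formed. Blinding does not repair this, because tolerability and benefit can differ by arm even when nobody knows the allocation.

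The two sections agree on the exclusion, so it is a deliberate rule and not a slip of wording. It also discards information: a participant who took too few doses but returned an end-of-treatment PSQI would have a usable outcome that the plan sets aside.

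The imputation sentence does not make up for this on the primary outcome. The PSQI is taken only at baseline and at the end of treatment, so a missing primary outcome will nearly always belong to someone already removed. The condition that missing at random be met is also something the observed data cannot establish.

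At stake is the main conclusion. The abstract says that the results will confirm efficacy, whereas a completer comparison answers a different question, and its bias cannot be gauged from the completers alone.

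**Working it through.** **Inputs from the protocol article.** Success 40% (placebo) and 70% (JTW); two-sided alpha 5%; power 80%; 1:1 allocation; 20% loss; 49 per group for analysis and 62 randomised (Sample size). Fisher's exact test (Statistical analysis).

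**1. The plan's own figure.** Two-proportion formula with mean proportion 0.55:

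[1.96 × √(2 × 0.55 × 0.45) + 0.842 × √(0.7 × 0.3 + 0.4 × 0.6)]² / 0.30² ≈ 42.

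With continuity correction: (42/4) × [1 + √(1 + 4/(42 × 0.30))]² ≈ 48.4, so 49. Then 49/0.8 = 61.25, so 62 per group and 124 in total. The stated figures reproduce. (The formula as printed gives 47.1, so 48; the difference does not matter here.) The design therefore expects to lose about 62 − 49 = 13 per arm.

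**2. Power of the planned completer analysis.** With 49 per group, 70% versus 40%, exact enumeration of Fisher's test gives 81.5%. The defect is bias, not nominal power.

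**3. Possible bias when the drug does nothing.** *Assumptions, not in the document:* true success 40% in both arms; every drop-out would have been a failure; loss split by arm as shown. Each split averages the stated 20%. Completer success = 0.40/(1 − loss). The false-claim rate is the exact probability that Fisher's two-sided p is at most 0.05 with JTW ahead.

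| Loss JTW / placebo | Completers analysed | Completer success | Spurious difference | False claim for JTW |
|---|---|---|---|---|
| 30% / 10% | 43 vs 56 | 57.1% vs 44.4% | +12.7 points | 21.8% |
| 25% / 15% | 46 vs 53 | 53.3% vs 47.1% | +6.3 points | 8.1% |
| 20% / 20% | 49 vs 49 | 50% vs 50% | 0 | 1.7% |
| 10% / 30% | 56 vs 43 | 44.4% vs 57.1% | −12.7 points | 0.05% |

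For reference, all 62 per arm at a true 40% give 1.7% in JTW's favour. The 12.7 points are 12.7/30 = 42% of the planned effect. If drop-out is unrelated to outcome, 43 versus 56 completers at 40% give 2.0%, so unequal loss alone does no harm; it must also be linked to outcome.

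**4. A check on the remedy.** Counting missing outcomes as failures is right by construction in step 3, so that comparison flatters it. Suppose instead that drop-out is random, true success is 40% in both arms, and loss is 10% JTW versus 30% placebo. Failure-counting then gives 0.40 × 0.90 = 36% versus 0.40 × 0.70 = 28%, and a false claim for JTW in 11.6% of trials.

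**5. Power with all 62 per arm analysed (Fisher).**
- If 70%/40% are completer rates and 20% per arm count as failures: 0.70 × 0.80 = 56% versus 0.40 × 0.80 = 32%, power 73.7%. Reaching 80% would take 66 per group by the normal approximation, or 75 with continuity correction.
- If 70%/40% hold for everyone randomised and outcomes are known: about 91%.

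**The case against.** Four points can be made for the plan or against too strong a criticism.

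- **Imputation.** A reader might infer that the imputation sentence contradicts the completer population. The document does not support that. A completer can lack a polysomnography night, a spectroscopy ratio, a blood value or single PSQI items, and imputing those within completers is coherent. What stands is narrower: for the primary outcome there is almost nothing left to impute.
- **Direction.** A reader might infer that the plan favours JTW, or that 21.8% is its error rate. Neither follows. The document gives no loss by arm. Equal loss under the same assumptions produces no bias, and if lack of benefit drives people out of the placebo arm, the bias runs against JTW. Treatment lasts one week with daily calls, so a 20-point gap in loss is an extreme case.
- **The usual remedy is not neutral.** Failure-counting can also produce a spurious benefit when loss differs by arm (step 4). This is correct, and it is why a single rule without sensitivity analyses would not be enough.
- **Data retrieval.** A reader might take the daily telephone calls as a ready source of PSQI scores from those who stop. The adverse-event section plans them for recording adverse events during treatment, and the PSQI is a self-completed questionnaire, so this would be a new procedure.

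None of this defends the exclusion itself. Nor is the population a detail left to an analysis plan: the protocol fixes it in two sections.

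**Conclusion.** Wrong as written. The rule selects participants on post-randomisation events and bars their collected data from the efficacy analysis of a randomised superiority trial. The rule is certain from the text; the size and sign of the bias are not. Under the stated assumptions the chance of a false claim for JTW ranges from 0.05% to 21.8%, against 1.7% with equal loss. That range illustrates how far the result could move and does not predict what will happen. Since the plan itself allows for losing a fifth of participants and names no other analysis, the point should be settled before the blind is broken.

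**What to change.** 1. **Participant drop-outs:** in the sentence "Their data will be collected in the case report form but will not be used for the final statistical analysis", delete everything after the mention of the case report form.
2. **Statistical analysis:** replace the population sentence with text such as: *The primary analysis includes all randomised participants in the group to which they were assigned, and uses every end-of-treatment PSQI collected, including from participants who stopped or did not comply.*
3. **Missing PSQI:** name one primary rule in advance for the binary endpoint, for example non-response. Add multiple imputation and a tipping-point analysis that varies the assumed success of missing participants in both arms and both directions, because non-response counting can itself mislead when loss differs by arm. Replace the condition that missing at random be met with a statement that it is assumed and tested by these analyses.
4. **Completers:** keep as a sensitivity analysis.
5. **Sample size:** say whether 70% and 40% describe completers or all randomised participants, and restate the power to match (about 74% or about 91% with Fisher's test at 62 per arm).

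**Cost.** Mostly wording and modest extra analysis. Two items are more than wording: obtaining the end-of-treatment PSQI from participants who stop needs its own procedure and should not rely on the adverse-event calls; and under the failure-counting reading, 124 participants fall short of 80% power, so the sponsor must accept that or revise the number.

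### Imputation depends on missing at random being met, which observed data cannot establish, so whether to impute is left open until the data are seen

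*Protocol article*

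**What the plan says.** Three statements in the Statistical analysis section of the protocol article bear on this point, in this order:

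- The population: "We define the analysis population as the enrolled participants who have successfully completed the trial".
- The look at missingness: "We will characterize the types of individuals who have missing data to better understand the nature the missing mechanisms".
- The rule: "We will use statistical models to impute missing values if the assumption of missing at random is met".

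The section gives no criterion for deciding that the condition holds and does not say what is done if it is judged not to hold. The primary analysis is fixed as follows: "For the primary outcome, we will use Fisher’s exact test to test the hypothesis at null: the treatment has the same efficacy as the placebo".

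Three other sections matter. Participant drop-outs says of those who leave: "Their data will be collected in the case report form but will not be used for the final statistical analysis". Sample size allows for losses of one in five ("Considering a 20% drop-out rate"), which takes 49 per group to 62. Blinding states that the statisticians do not know the allocation during the study.

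**The concern.** MAR means that, given what was recorded, whether a value is missing does not depend on the value itself. MNAR means that it does. The difference lies in values nobody has. Comparing participants with and without missing data can show that missingness is related to recorded characteristics, and so argue against missing completely at random. No such comparison can show that MAR holds rather than MNAR.

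The rule uses MAR as a switch all the same. Two analysts with the same dataset could read the description of missingness differently. One would impute and the other would not, and both would have followed the text. The handling of missing outcomes is therefore not fixed in advance.

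The switch also gives no help where help is most needed. If MAR is doubted, the only course the text leaves is not to impute, which means complete cases. A completer comparison is sound if, within each arm, missingness is unrelated to outcome. Doubting MAR gives no reason to believe that. Such doubt calls for a sensitivity analysis; dropping imputation does not answer it.

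**Working it through.** **Inputs.** From Sample size: assumed success 70% (JTW) and 40% (placebo), two-sided 5% level, 80% power, 20% drop-out, 62 per group. From Statistical analysis: Fisher's exact test. The observed counts below are assumptions chosen to match these figures.

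**The plan's own figure.** The usual two-proportion formula gives n = [1.96·√(2·0.55·0.45) + 0.842·√(0.7·0.3 + 0.4·0.6)]² / 0.3² ≈ 42 per group. With continuity correction this becomes 49. Then 49/(1 − 0.2) = 61.25, rounded up to 62, and 2 × 62 = 124. The stated total reproduces and is not affected by this point.

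**Can the condition be evaluated?** Take 62 per arm with 12 missing in each (about 20%), and 35/50 versus 20/50 successes among those observed. These observed counts stay the same in every row below; only the unseen outcomes change. The difference is x₁/n₁ − x₀/n₀, and p is two-sided Fisher.

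| Missing outcomes | JTW | Placebo | Difference | p |
|---|---|---|---|---|
| Left out (completers) | 35/50 | 20/50 | 30.0 points | 0.0046 |
| Filled in at each arm's observed rate | 43/62 | 25/62 | 29.0 points | see note |
| All failures | 35/62 | 20/62 | 24.2 points | 0.011 |
| JTW all failures, placebo all successes | 35/62 | 32/62 | 4.8 points | 0.72 |

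Note: row two adds 12 × 0.7 = 8.4, taken as 8, and 12 × 0.4 = 4.8, taken as 5. A single fill-in overstates precision, so its p-value is not used.

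Rows one and two stand for the two positions of the switch. They differ by 1 point, and that is rounding; imputation from baseline covariates could shift it further by an amount the documents do not allow one to estimate. Rows three and four are not options under the sentence. They show what else the same data permit.

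**A closer result.** Assume 31/49 versus 20/49 observed and 13 missing per arm.

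- Completers: 11/49 = 22.4 points, p = 0.043.
- Filled in at each arm's observed rate (8 and 5 successes): 39/62 versus 25/62, 22.6 points.
- Missing as failure: 31/62 versus 20/62, 17.7 points, p = 0.068.
- Both arms filled in at about 40% (5 and 5): 36/62 versus 25/62, 17.7 points, p = 0.072.

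Again the two switch positions nearly agree, while other assumptions that fit the same data fall on the other side of 0.05.

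**The case against.** The strongest reply has five parts.

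1. **The planned 20% are not governed by this sentence.** Drop-outs are removed by the Participant drop-outs section and by the completers-only population, so as written imputation reaches only incomplete values among completers. This stands. It means the rule has little to act on today and that the fix must cover those passages too. It does not make the condition workable.

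2. **The effect is small.** From the table a reader might infer that the rule can move the estimate by about 25 points (30 to 5). The documents do not support that. The sentence offers MAR-based imputation or none, which differ by about 1 point here. The 25 points are an extreme bound over assumptions that the rule never invokes.

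3. **No fallback is stated.** A reader might take complete cases as the written fallback. It is only implied, by the absence of any other instruction and by the population definition.

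4. **Blinding limits abuse.** The statisticians are stated to be blinded, so a choice made after seeing the data would not be made knowing which arm it favours. A reader might also infer an inflated type I error, and the check that was run does not show it. With 40% success in both arms and 20% loss completely at random, taking the smaller p of completers and missing-as-failure rejected in 4.7% of 20,000 simulated trials. That check does not test the switch itself. Blinding does not make the rule determinate either.

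5. **Details belong in an analysis plan.** The imputation model and sensitivity tables may well be there, and their absence from an article is no fault. But an analysis plan could not make the condition verifiable; it would have to replace it. Reading the condition loosely, as MAR being plausible, still leaves a judgement made after the data are seen.

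**Conclusion.** The point holds in a limited form. The protocol states a condition that observed data cannot settle and lets it decide whether missing values are imputed, so that decision is left until the data have been seen, by statisticians stated to be blinded. The implied alternative, complete cases, gives no general protection when MAR is doubted.

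The switch may itself move the point estimate little: about 29 versus 30 points in the assumed example. The larger matter is that the same data are compatible with 24 points (missing as failure, p = 0.011) or, at an extreme bound, 5 points (p = 0.72), and neither position of the switch would show it. These figures rest on assumed counts of 35/50 and 20/50, on 12 missing per arm, and on drop-outs being brought into the analysis, which the current text does not do.

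**What to change.** Replace the conditional sentence with an unconditional rule. For all randomised participants, missing end-of-treatment PSQI is multiply imputed by arm from baseline PSQI and other baseline measures, with MAR as a stated working assumption, and response is then derived from the imputed score. The treatment effect is pooled as a risk difference or a logistic estimate, because Rubin's rules combine estimates with standard errors and do not pool Fisher exact p-values.

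Reconcile this with the exclusion of drop-outs in Participant drop-outs and with the completers-only population in Statistical analysis; otherwise the imputation will have few primary outcomes to act on.

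Prespecify two sensitivity analyses: missing counted as failure in both arms, where Fisher's exact test can still be used, and a delta-adjusted or tipping-point analysis. Keep the description of who has missing data as description only.

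The cost is revised wording in two sections and modest extra programming, with no new kinds of measurement. The downside is that the primary test is no longer a single Fisher's exact test on completers. The change should be settled before the blinding codes are revealed.
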